### **Sevoflurane group （Group A）**

Propofol is used only during the induction of anesthesia at sevoflurane group. Sevoflurane is controlled at a concentration of 0.6-2% in the exhaled sevoflurane. The use of propofol (except when induction of anesthesia) is prohibited during anesthesia, but there are no restrictions on other drugs.

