## Criteria for Discontinuation of Protocol Treatment

## Discontinue protocol treatment if adverse events are observed in which each group-assigned drug is suspected.

# Expected adverse events

- 1. **Expected adverse events**
     1. **Adverse events expected with the drug**

According to the drug package insert

- - 1. **Adverse reactions and surgical complications expected by surgery**

1. Anesthesia-related complications

Fever^*1^, allergic reaction, inability to secure airway, acidosis^*1^, hyperkalemia^*1^, delirium, hoarseness, hematoma^*2^, catheter-related infection^*3^

*1 Items assuming malignant high fever expected as a complication of general anesthesia

*2 Items assuming epidural hematoma and spinal cord subarachnoid hematoma expected as complications of epidural anesthesia

*3 Items assuming epidural abscess and spinal cord subarachnoid abscess expected as complications of epidural anesthesia

1. Surgical complications

Damage to other organs, biliary fistula (about 10%), postoperative hemorrhage, infection (about 10%), liver failure (less than 0.1%), pulmonary embolism, death (less than 0/1%)

- 1. **Evaluation of adverse events/reactions**

To assess adverse events/reactions, the "JCOG postoperative complications criterion (Clavien-Dindo classification)" is used.

- - 1. **Grading of adverse events**

When grading adverse events, grading is the closest to the definition of grades 0 to 4, respectively. Also, when a specific treatment is described in grade, grading is performed from the clinical necessity. For example, the patient's pleural effusion may be increasing and the patient may refuse oxygen inhalation or chest drainage despite the indication of the situation. In such cases, grading is based on a medical judgment of what should be done, not what was actually done.

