# Evaluation items, clinical tests, and evaluation schedule

- 1. **Items to be collected before registration (using information from the anesthesiology preoperative outpatient clinic)**

Patient background (age, sex, primary cancer type, preoperative complications [Charlson Index], presence or absence of preoperative chemotherapy [drug used if performed], allergic history), ASA-PS, biochemical tests (AST, ALT, Bil)

- 1. **Observation period**

The observation period will be up to 28 days after surgery to assess postoperative complications in both groups. If protocol treatment is discontinued in any group, no observation period is set.

- 1. **Items to be collected during the treatment period**

Surgical method, anesthesia method, operative time, anesthesia time, number and total weight of resected liver, total ischemic time, intraoperative blood loss, intraoperative fluid/transfusion volume, intraoperative urine volume.

- 1. **Evaluation items after the end of treatment**
     1. **Primary outcome**
- Liver damage:

Assessed with the highest value of AST 3 days postoperatively.

In addition, the results of postoperative biochemical tests (tested daily for 3 days after surgery) that are usually performed in clinical practice will be used, and blood collection and testing for this study will not be performed.

- - 1. **Secondary outcome**
- Liver damage

As a particularly important secondary endpoint, the highest ALT value at 3 days postoperatively will be evaluated. In addition, the results of postoperative biochemical tests (tested daily for 3 days after surgery) that are usually performed in clinical practice will be used, and blood collection and testing for this study will not be performed.

- Early postoperative liver function evaluation

Assessed at the highest value of Bilirubin 3 days postoperatively. In addition, the results of postoperative biochemical tests (tested daily for 3 days after surgery) that are usually performed in clinical practice will be used, and blood collection and testing for this study will not be performed.

- Postoperative adverse event

JCOG postoperative complication criteria (Clavien-Dindo classification) Collect postoperative complications of grade II or higher for 28 days postoperatively.

- 1. **Evaluation Schedule**

|  | pretreatment | postoperative | | | |
| --- | --- | --- | --- | --- | --- |
|  | Anesthesiology outpatient | Day 1 | Day 2 | Day 3 | 〜 28 days |
| Characteristics | ○ | - | - | - | - |

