The maximum AST value within 3 days after surgery. In a retrospective study of metastatic liver tumor resection in the last 2 years, it was confirmed that the highest value in the early postoperative period was achieved within 3 days after surgery, so it was set as the highest value within 3 days after surgery.

- Secondary endpoint

Set the highest ALT value within 3 days postoperatively as an important secondary endpoint. As other endpoints, the JCOG postoperative complication criterion (Clavien-Dindo classification) Grade II or higher postoperative complications and the highest Bil-value within 3 days after surgery as a liver function evaluation are used.

1. **Reporting Adverse Events and Defects**

In the event of a "serious adverse event" or "unexpected adverse event", the attending physician should report it to the Research Secretariat/Principal Investigator. The events listed in the package insert are not counted as adverse events in this study.

Report to the Minister of Health, Labour and Welfare on adverse reactions based on the Act on Securing Quality, Efficacy and Safety of Pharmaceuticals and Medical Devices (Address: Safety Information Division, Safety Department 1, Pharmaceuticals and Medical Devices Agency, [contact], Email: [[contact])](mailto:[contact])17)「,)^[17)](mailto:[contact])17)「,)^[,](mailto:[contact])17)「,) Based on the "Ethical Guidelines for Medical Research Involving Human Subjects" (Ministry of Education, Culture, Sports, Science and Technology / Ministry of Health, Labor and Welfare Notification No. 18), the director of the medical institution reports unexpected serious adverse events to the Minister of Health, Labour and Welfare, etc., and the medical institution to the company to communicate side effects to the company, it is the responsibility of the principal investigator to appropriately report to the head of the medical institution at each facility.

- 1. **Emergency Reportable Adverse Events**

Adverse events that fall under any of the following are designated as "serious".

1. Any death during protocol treatment, regardless of whether or not there is a causal relationship with protocol treatment.
2. Death after completion of protocol treatment and a causal relationship with the protocol cannot be ruled out. Obvious death from primary disease does not apply.
3. Life-threatening:

Grade 4 non-hematologic toxicity or equivalent in CTCAE v4.0.

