When hospitalization for treatment or an increase in the duration of admission is required.

However, if hospitalized for the following purposes, it will not be treated as a serious adverse event.

Hospitalization to reduce the burden on patients visiting from remote locations

Pre-planned hospitalization

1. Permanent or severely impaired or dysfunctional.
2. Aplastic anemia. Myelodysplastic syndrome, secondary cancer, or other congenital diseases or abnormalities in later generations
3. Other serious medical events.

Those that do not fall under any of the items 1 to 6 above, but are judged to be medically important by the research responsible physician

- 1. **Reporting Obligations and Reporting Procedures for the Principal Investigator**
     1. **Emergency Report**

When an adverse event that is subject to emergency reporting occurs, the attending physician will promptly notify the Secretariat/Principal Investigator. At that time, care shall be taken not to include the medical record number, etc.

1. Upon learning of an adverse event of CTCAE v4.0-JCOG or Clavien-Dindo Grade 3 or higher, or any other adverse event that is judged to be medically significant, the attending physician should promptly report it to the Secretariat/Principal Investigator.
2. Additional Reporting

When new information is obtained after the above report, the information will be added to the prescribed form and reported as needed.

- - 1. **Report to the head of the medical institution**

When an adverse event that is subject to emergency reporting occurs, the principal investigator reports it to the head of the medical institution as a "serious adverse event" in the "Ethical Guidelines for Medical Research on Human Subjects" in accordance with the regulations of the medical institution.

- - 1. **Reporting to other reporting destinations**

Reporting of product safety information for pharmaceuticals, medical devices, regenerative medicine, etc: Based on Article 68-10, Paragraph 2 of the Act on Securing Quality, Efficacy and Safety of Pharmaceuticals, Medical Devices, etc., information that is deemed necessary to be reported shall be appropriately reported to the Minister of Health, Labour and Welfare in accordance with the regulations of medical institutions.

- 1. **Responsibilities of the Principal Investigator/Secretariat**
     1. **Determining whether registration is suspended and emergency notification is required**

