As an important secondary endpoint, the highest ALT value within 3 days postoperatively for ischemia-reperfusion injury was compared in two groups by t-test, and a significant difference of less than 0.05 was statistically significant. For postoperative complications within 28 days, the Fisher test compares the two groups, with a significant difference of less than 0.05 as statistically significant. Regarding liver function, the highest bilirubin value within 3 days after surgery was compared in two groups by t-test, and a significant difference of less than 0.05 was considered statistically significant.

- 1. **Final Analysis**

In addition to the analyses described in 10.1 and 10.4, multivariate logistic analyses are performed to exclude the effects of non-anesthesia methods on IRI.

- 1. **End of research**

The research will end with the publication of all papers related to this study.

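### The sentence that stops package-insert events from counting as adverse events contradicts the protocol's own expected-event, discontinuation and reporting rules, and should be replaced

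*Protocol*

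**What the plan says.** Under Reporting Adverse Events and Defects, the protocol first asks the attending physician to report events that are either serious or unexpected. The next sentence reads: "The events listed in the package insert are not counted as adverse events in this study". It does not say which drug's insert is meant.

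Other parts of the protocol bear on the same events:

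- **Expected adverse events.** The entry for events expected with the drug reads in full "According to the drug package insert".
- **Criteria for Discontinuation of Protocol Treatment.** "Discontinue protocol treatment if adverse events are observed in which each group-assigned drug is suspected".
- **Emergency Reportable Adverse Events.** The list of serious events opens with "Any death during protocol treatment, regardless of whether or not there is a causal relationship with protocol treatment".
- **Emergency Report.** Prompt notification is due "Upon learning of an adverse event of CTCAE v4.0-JCOG or Clavien-Dindo Grade 3 or higher", and also for other medically significant events.
- **Secondary outcome, under the heading for postoperative adverse events.** "Collect postoperative complications of grade II or higher for 28 days postoperatively". Section 3 (Criteria and definitions) uses the same term for Grade 2 or higher complications.
- **Analysis in secondary endpoints.** "For postoperative complications within 28 days, the Fisher test compares the two groups", at the 0.05 level.

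**The concern.** Whether an event is listed in a package insert normally settles one question: is it expected? It does not settle whether the event is an adverse event. The protocol's sentence merges the two. Someone who follows it exactly would leave out the known reactions to the study drugs, including serious ones, although other sections require those same events to be recognised, acted on and reported.

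Safety reporting is at stake first. The yearly report of adverse events to the hospital director (Report on the progress of clinical research) would inherit the gap. The discontinuation rule is also affected, because it depends on the term adverse event. Discontinuation in turn decides whether a per-protocol analysis is run and who is in it (Define the target population).

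The secondary complications endpoint could be affected as well, since it carries the same name as the thing being excluded. Two data collectors could then code the same patient differently, and each could cite the protocol.

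**Working it through.** The protocol gives no figure on this point to reproduce. The check is a comparison of its sections, followed by a short calculation for scale.

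**Step 1. Compare the exclusion with each rule.**

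| Rule | Treatment of a listed event | Consistent with the exclusion? |
|---|---|---|
| Expected adverse events | The insert is the source of the adverse events expected with the drug | No: the same list is called adverse events here and not adverse events there |
| Duty to report serious or unexpected events | A serious event is reported even if expected | No: a serious listed event is required by one sentence and excluded by the next |
| Death during treatment; prompt report at Grade 3 or higher | No exemption for listed events | No, if the exclusion is read literally |
| Discontinuation on suspected drug adverse events | No exemption for listed events | No: read literally, a known reaction is not an adverse event and does not meet the trigger |
| Grade 2 or higher complications endpoint | Defined by the JCOG/Clavien-Dindo criteria, no exclusion stated | Unclear: same term, but the reach of the exclusion is not stated |

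**Step 2. Could the exclusion act differently by arm?** In group A, "Propofol is used only during the induction of anesthesia at sevoflurane group", with sevoflurane for maintenance. Group B receives propofol throughout, and sevoflurane is prohibited. Both arms therefore receive propofol and only group A receives sevoflurane. Both also share rocuronium, fentanyl and/or remifentanil, sugammadex and hydrocortisone.

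- If the inserts of all drugs given apply, the lists overlap heavily and the fixed difference is sevoflurane.
- If only the assigned drug's insert applies, each arm has its own list.

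Unequal exclusion is possible under either reading. Its extent cannot be determined without the inserts.

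**Step 3. Scale of the endpoint.** Inputs: 28 patients per arm, 56 in total (Planned number of registrations), and a Grade 2 or higher rate of about 1% (Rationale for setting up endpoints).

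- Expected events: 56 × 0.01 = 0.56.
- Chance of at least one event: 1 − 0.99^56 = 0.43.

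With a events in one arm of 28 and none in the other, the two-sided Fisher p-value is 2 × C(28, a) / C(56, a) for a ≥ 1:

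| Events | Calculation | p |
|---|---|---|
| 1 v 0 | 2 × 28 / 56 | 1.0 |
| 2 v 0 | 2 × 378 / 1,540 | 0.49 |
| 5 v 0 | 2 × 98,280 / 3,819,816 | 0.051 |
| 6 v 0 | 2 × 376,740 / 32,468,436 | 0.023 |

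At the 1% rate, losing one or two events would leave the test non-significant either way, although it could empty the descriptive safety table. A single event could move p across 0.05 only at higher counts with a one-sided split. The list of surgical complications gives about 10% each for biliary fistula and infection, that is 56 × 0.10 = 5.6 expected events of each. Those are listed apart from drug events, however, and nothing shows that the exclusion would remove them.

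**The case against.** The strongest reply is that the sentence belongs to a reporting chapter and directly follows the duty to report unexpected events. Its author may have meant only that listed events are not unexpected. The complications endpoint is defined elsewhere without any such exclusion, and the main analysis, sample size and primary endpoint (peak AST) are untouched. Both drugs are described as standard treatment.

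Much of this stands, and it rules out several stronger inferences a reader might draw:

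- **That deaths would go unreported.** The list of serious events covers any death during protocol treatment whatever the cause, and the Grade 3 rule and statutory product-safety reporting have no listed-event exception. The text is in conflict; it does not establish that deaths would be missed.
- **That a known reaction could never lead to a change of treatment.** The opening of Treatment Plan and Treatment Change Criteria provides for changes on the anesthesiologist's medical judgment, whatever the event is called.
- **That the Grade 2 or higher comparison is biased, with a different list deleted in each arm.** The endpoint definition contains no exclusion, no insert is reproduced, and group A also receives propofol at induction.
- **That losing one or two events would change the safety result.** At the protocol's own event rate the Fisher test does not move to significance.

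The reply does not rescue the sentence itself. If it was meant to concern expectedness only, it says something broader than intended. If it was meant literally, it conflicts with the sentence before it and with three other rules.

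**Conclusion.** The sentence is wrong as written. It is current text, unlimited by grade, seriousness or drug, and it contradicts the expected-event entry, the duty to report serious or unexpected events, the Grade 3 or higher rule and the discontinuation trigger. Following it could leave serious but listed drug reactions unrecorded or unreported.

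The effect on the Grade 2 or higher comparison is a risk. It arises because the endpoint shares the term adverse event, and it could fall unequally because only group A receives sevoflurane. Its size cannot be given without the inserts. The scale figures of 0.56 expected events and a 43% chance of any rest on the protocol's 1% rate and 56 patients. They show only how sparse the endpoint is, not how much would be lost.

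**What to change.** Replace the sentence with wording such as: *Package-insert events are recorded, graded and reported if serious; listing only determines that an event is classed as expected.*

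State alongside the endpoint definition that the Grade 2 or higher comparison counts all events regardless of listing.

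Reconcile the discontinuation wording with the revised sentence, so that the term adverse event means the same thing in both places. The clinical content of that rule is for the investigators to settle; no particular rule is proposed here.

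This is a short protocol amendment needing ethics committee approval. It adds no tests or patients and does not touch the primary analysis. The downside is slightly more event recording. It is best made early, because events not recorded at the time may be hard to recover later.

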# 2. Background and rationale for the test plan

## Patient

### Background

In hepatectomy, the Pringle method (a method of temporarily blocking blood flow in the hepatic artery and portal vein system by clamping the hepatic duodenal ligament with forceps or the like) is widely used.^1),2)^ Pringle method reduces intraoperative bleeding, but hepatocytes undergo ischemia-reperfusion injury (IRI). In addition, highly invasive surgery such as hepatectomy causes strong oxidative stress. IRI and oxidative stress cause postoperative liver damage^3)^. General anesthesia is required for hepatectomy, but there are two methods: general anesthesia using volatile anesthetic(VA) and general anesthesia using only intravenous anesthesia (total intravenous anesthesia: TIVA). Volatile anesthetics have been noted to have an ischemic resistance effect. During cardio-plumonary bypass, clinical utility has been recognized not only for reducing myocardial damage but also for reducing postoperative complications. ^4)^ On the other hand, propofol used in TIVA has anti-oxidant effect..^5)^ The results of previous studies in the field of liver surgery are heterogeneous. ^5)-12)^We assess the cause of heterogeneity include interventions for multiple factors affecting IRI(intervention in both ischemia and anesthetics) and heterogeneity in the subjects of study (differences in background liver function, differences in the method of application of the Pringle method).

The golden standard of the marker of liver damage ins transaminases(AST and ALT).^13)^ In many clinical studies, postoperative transaminases are used to evaluate liver damage. ^5)-11)^。However, there are many factors affecting transaminase(for example, the size of the resected liver, the time of hepatic ischemia, liver cirrhosis, fatty liver). Thus, we select the metastatic liver tumor resection with relatively little variation in these factors. And We limit the cases to which the number of tumors less than 5 and scheduled resection size with less than 5 Couinaud segments.

If there are differences in intraoperative anesthetics in this study, selecting the appropriate anesthetic may contribute to reducing liver damage after hepatectomy.

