### Summary of the risk-benefit balance and risk-benefit balance between standard and study treatments

As both VA and TIVA are standard therapy, there is no significant risk-benefit imbalance between VA and TIVA. This study is a superiority test, but it is unclear which drug has superiority.

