**3. Criteria and definitions used in this test**

- 1. **Types of hepatectomy**
- major resection：Hepatectomy of 3 or more areas in the Couinaud classification
- minor resection：Hepatectomy of less than 3 areas in the Couinaud classification
  1. **ASA-PS (American Society of Anesthesiologists physical status)**

It is a classification of preoperative general condition defined by the American Society of Anesthesiologists

　Class 1：No complications other than the disease causing surgery

　Class 2：Normal activities of daily living but mild systemic illness

　Class 3：A condition with a high degree of systemic disease that restricts activities of daily living

　Class 4：Conditions requiring life-threatening systemic diseases

　Class 5：A dying condition in which the possibility of saving lives is low even after surgery

　Class 6：Conditions diagnosed as brain dead (brain-dead organ transplant donors)

- 1. **Charlson Index^14)^**

Score to assess for preoperative complications^15)^

- 1. **Postoperative adverse event**

JCOG postoperative complications criteria (Clavien-Dindo Classification) version 2.0 with grade 2 or higher.

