Upon receiving the report from the Principal Investigator, the Research Office will judge the urgency, importance, degree of impact, etc. of the report content, and if necessary, entrust the hospital director and the director to determine whether it is necessary to suspend registration or to notify the facility of information urgently.

- - 1. **Notifying Researchers in the Facility**

The Secretariat/Principal Investigator shall notify the Researcher in the Institute of the decision of the Secretariat/Principal Investigator in writing (e-mail is acceptable) regarding serious adverse events.

1. **Statistics**
   1. **Main analysis and criteria**

The main analysis is to compare the highest AST values within 3 days postoperatively in groups A and B by t-test, and judge a significant difference of less than 0.05 to be statistically significant. As a criterion for determining that the degree of IRI differs depending on the anesthetic, a difference of about AST 300 U / L was observed. This was based on the idea that a difference of about AST300U/L would have a significant impact on clinical anesthetic selection. If necessary, sensitivity analysis will include a population of patients who have completed protocol treatment (PPS), or a population of all randomized cases and supplemented with the worst values observed in groups A and B in cases where primary endpoint data are missing.

- 1. **Planned number of registrations, registration period, tracking period**

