Currently, the ischemic method that alleviates IRI is considered to be the intermittent ischemia method, and in consideration of the effect of IRI on the whole body, the intermittent ischemia method is also adopted in our hospital. However, previous studies used continuous ischemia, which strongly expresses IRI, except for one group in the 2012 Beck-Schimner et al. trial, and the mean, median, standard deviation, and quartile values of postoperative AST values are likely to differ from the results of this postoperative ischemia. Therefore, we mainly referred to the results after intermittent ischemia and the results of our retrospective studies in the previous study, and the other studies were only secondary references. First, postoperative AST was treated as normally distributed. Next, clinically, it was judged that a difference of about 300 U/L of AST had a significant impact on anesthetic drug decision. The standard deviation of AST is expected to be 300 U/L. Finally, the significance difference was set to 0.05 and the detection power was set to 0.8. Under these conditions, 28 patients in each group (56 patients in total) were calculated to be required. The number of such surgical cases is about 40 per year at our single facility, and about 70% of them are liver tumor resection in less than 5 places and the liver is completely removed less than 5 areas of Couinaud. The annual enrollment rate for this trial is estimated to be around 17, with an expected participation consent acquisition rate of 60%, and the planned registration period is expected to be 3 years and 3 months. The follow-up period shall be 28 days postoperatively, which is the definition of postoperative complications.

- 1. **Interim analysis and early discontinuation of the study**

　　　　　No early discontinuation of interim analyses or trials is planned.

- 1. **Analysis in secondary endpoints**

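### The primary AST comparison is an unadjusted t-test although prognostic baseline information is available before randomisation; it is valid, but may give away precision

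*Protocol*

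**What the plan says.** Main analysis and criteria (Statistics, 10.1) fixes the method: "The main analysis is to compare the highest AST values within 3 days postoperatively in groups A and B by t-test". The analysis of secondary endpoints uses the same unadjusted test for peak ALT and peak bilirubin. The criterion for a relevant effect is on the original scale: "it was judged that a difference of about 300 U/L of AST had a significant impact on anesthetic drug decision".

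Other sections bear on this choice:

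- Background: "there are many factors affecting transaminase(for example, the size of the resected liver, the time of hepatic ischemia, liver cirrhosis, fatty liver". The protocol responds by restricting entry to metastatic tumours, with fewer than five tumours and a planned resection of fewer than five Couinaud segments. The eligibility criteria also cap preoperative AST and ALT below 100 IU/L.
- Criteria and definitions: major resection is "Hepatectomy of 3 or more areas in the Couinaud classification", and anything smaller is minor.
- Items to be collected before registration: these include "biochemical tests (AST, ALT, Bil".
- Randomization: blocks are used, with no adjustment factor.
- Final Analysis: multivariate logistic analyses are added to remove the influence of factors other than anaesthesia. Neither the binary outcome nor the covariates are given.

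**The concern.** The protocol itself identifies a source of variation in the primary endpoint that is unrelated to anaesthesia, and its entry limits do not remove it. A resection of three or four segments is major under the protocol's definition and still eligible, so both classes can be enrolled. With no stratification and no adjustment, variation due to planned extent and to the starting AST stays in the error term. A chance imbalance between the arms stays in the estimated difference.

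The stake is the width of the confidence interval around a difference that is to be judged against 300 U/L. The planned logistic analysis does not help: it would need AST to be cut at a threshold that is not given, and it estimates an odds ratio rather than a difference in U/L.

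**Working it through.** **Inputs.** Difference 300 U/L ("it was judged that a difference of about 300 U/L of AST had a significant impact on anesthetic drug decision"). SD: "The standard deviation of AST is expected to be 300 U/L". Error rate and power: "Finally, the significance difference was set to 0.05 and the detection power was set to 0.8". Sidedness is not stated; two-sided is assumed because the protocol says "This study is a superiority test, but it is unclear which drug has superiority". Planned size: 28 per arm. R², the share of peak-AST variance explained by the baseline covariates within arms, is not in the document and is assumed to lie between 0 and 0.4.

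**The plan's own figure.** Normal formula: n = 2(1.96 + 0.842)² × (SD/difference)². At 300/300 this is 15.7, so 16 per arm (17 by the t formula), not 28. At SD 400 it is 15.7 × (4/3)² = 27.9, so 28. The mismatch is a separate issue. It matters here only because it shows which SD would make 28 the right number, so results are given at both.

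**Unadjusted t-test, 28 per arm, SD 300.** SE = 300 × √(2/28) = 80.2. With 54 degrees of freedom, half-width = 2.005 × 80.2 = 161 U/L. Power for 300 U/L (noncentral t) is 0.957.

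**With two baseline covariates.** Residual SD = SD × √(1 − R²), with 52 degrees of freedom. Example at R² = 0.4: 300 × √0.6 = 232.4; SE = 62.1; half-width = 2.007 × 62.1 = 125 U/L. The middle SD is the root mean square of the preliminary SDs in the endpoint rationale, √((460² + 178²)/2) = 349, with equal group weights assumed.

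| | SD 300 (protocol): half-width; power | SD 349 (preliminary data): half-width; power | SD 400 (assumed): half-width; power |
|---|---|---|---|
| Unadjusted | 161; 0.957 | 187; 0.89 | 214; 0.79 |
| R² = 0.05 | 157; 0.965 | 182; 0.90 | 209; 0.81 |
| R² = 0.1 | 153; 0.972 | 178; 0.91 | 204; 0.83 |
| R² = 0.2 | 144; 0.984 | 167; 0.94 | 192; 0.87 |
| R² = 0.3 | 135; 0.992 | 157; 0.97 | 180; 0.91 |
| R² = 0.4 | 125; 0.997 | 145; 0.98 | 166; 0.94 |

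**Cost if the covariates explain nothing.** Two lost degrees of freedom move the half-width at SD 300 from 160.7 to 160.9 U/L. The table leaves out a small average penalty for estimating the two coefficients, about 2/(56 − 2 − 3) = 2/51 = 3.9% of the variance, or about 2% of the SE. Including it, the SD 300 half-width is about 164 U/L at R² = 0 and 127 U/L at R² = 0.4. Adjustment breaks even on average at R² of about 0.04, since 1 − 1/1.039 = 0.038.

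**Chance imbalance, for illustration.** The document gives no proportion of major resections. If 22 of 56 patients had one, the hypergeometric probability that the arms differ by six or more major resections (6/28 = 21 percentage points) is 17%.

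**The case against.** The other side has a good case, and most of it limits the size of the point.

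- **Validity.** A reader might infer that the t-test is biased or that chance imbalance makes it wrong. It does not: randomisation keeps the test unbiased, and its standard error already allows for imbalance on average.
- **Power.** A reader might infer that the trial is underpowered without adjustment, or that power would rise by up to 16 percentage points. That gain needs a standardised effect of 0.75, which means SD 400. The protocol states 300/300, where unadjusted power is already 0.957 and the gain at R² of 0.1 to 0.4 is 1.5 to 4 points.
- **Strength of the predictors.** A reader might take the Background as calling these predictors strong. It says only that several factors affect transaminases, gives no strength, and does not list preoperative AST among them. Entry is restricted so that these factors vary little, and starting AST is capped below 100 IU/L against an expected peak SD of 300. R² may therefore be small, and values near zero belong in the range. Resection extent supports the point better than starting AST does.
- **Availability.** Scheduled major/minor extent is not a listed data item. Eligibility confirms only fewer than five segments, and the extent data that are listed are operative, hence after randomisation.
- **Adjustment already planned.** The logistic analysis shows that the sponsor sees a need to adjust. With no outcome or covariates defined, it does not do that job for the AST difference.

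All but the last of these stand as limits. None removes the gap: information available before allocation is unused, and using it costs very little.

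**Conclusion.** The point holds as an efficiency improvement, not as an error. With 28 per arm and an assumed R² of 0 to 0.4, adjustment would leave the interval essentially unchanged at the low end. At the high end it would narrow the half-width by about 22%: from 161 to 125 U/L at the protocol's SD, or from 214 to 166 U/L at SD 400. Under the protocol's own inputs the benefit is almost entirely a narrower interval, since power is already high. A material power gain depends on the true SD exceeding 300. The preliminary SDs of 460 and 178 make that plausible but do not establish it. The size of the benefit is uncertain because the document gives no R²; that the plan is unadjusted, unstratified and has baseline values to hand is not in doubt.

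**What to change.** Replace the primary t-test in 10.1 with a prespecified linear-model ANCOVA of peak AST on treatment, preoperative AST and scheduled major/minor resection (the protocol's own categories). Keep the outcome in U/L so that the adjusted difference still answers the 300 U/L criterion; a log model would estimate a ratio instead. Keep the unadjusted t-test as a supportive analysis. Use the same model for peak ALT and peak bilirubin, each with its own preoperative value.

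Take resection class from the operation scheduled at registration. State that the primary model does not adjust for measures taken after randomisation, such as resected weight or ischaemic time.

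Cost: one sentence in the protocol, two degrees of freedom, and one added field on the registration form for scheduled major/minor extent. No extra patients or blood tests are needed.
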